#### Primary outcomes

We have two primary outcome measures to allow us to evaluate the effect of the intervention on violence prevention at the level of (1) the teacher and (2) the children. Both measures involve observations by independent observers blind to the study design, hypothesis and group status.

Observations of teachers’ use of violence against children. These take place over two school days. Observations are continuous over one school day and for five 20 min intervals spread over the second school day linked to the schedule for class-wide observations (see below). Event recording will be used to record each use of corporal punishment, verbal abuse, and other abuse (eg, intimidation) by teachers. These behaviours are defined in an observation manual based on definitions used in Jamaican preschool classrooms previously.^5^ Teachers’ use of violence will be coded as a binary variable for analysis, with teachers coded as 1 if they use violence versus 0 if they do not. If the percentage of teachers using violence is more prevalent than anticipated and/or has wide variability in scores, then the variable will be coded as a count using three to four categories to represent the spread of the data.

Observations of class-wide child aggression. These take place over five 20 min intervals spread over one school day, and is based on a rating scale used previously in Jamaican preschool classrooms.^5^ At the end of each 20 min interval, observers rate the overall level of children's aggression in the classroom on a seven-point rating scale. The mean score over the five observations will be used in the analysis. Ratings of classroom aggression during the early childhood years predict growth in child aggression over time.^20^

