### Sample size

The trial has two primary outcomes: level of class-wide aggression and violence against children. Using Tukey's method of correction for multiple testing,^33^ we require a significance level of 0.036 in each individual test to keep a Family-Wise Error Rate of 0.05.

Level of class-wide aggression. In a parallel group design, 72 classes in each group are sufficient to detect an ES of 0.5 SD, with 81% power at 0.05 level of significance. With a cluster size of three (3 classrooms/school), and assuming an intraclass correlation (ICC) of 0.25, the design effect is 1.5 (design effect=1+(cluster size–1)×ICC)) giving a required sample size of 108 classrooms per group, which yields 36 schools per group. We will recruit 38 schools (114 classrooms) per group (76 schools in total) to allow for 9% teacher loss.

Violence against children by teachers. In a parallel group design, 90 classes in each group are sufficient to detect a reduction from 60% to 35% with 87% power at 0.05 level of significance. With a cluster size of three (3 classrooms/school) and an ICC of 0.1 (based on data from our efficacy trial), the design effect is 1.2, giving a required sample size of 108 classrooms per group, which yields 36 schools in each group. As mentioned above, we will recruit two additional schools per group.

The analyses of the secondary outcomes is considered exploratory, and the significance level of the tests will not be adjusted for comparisons of multiple outcome.

Classroom and teacher-level measures. Similar to the primary outcome of level of classwide aggressions, we have 85% power at a 0.05 level of significance to detect a difference of 0.5 SD on the quality of the classroom environment and on teacher depression, self-efficacy and burn-out.

Child-level measures. In a parallel group design, 252 children in each group are required to detect a difference of 0.25 SD with 80% power at 0.05 level of significance. With 11 children per school, and an estimated intracluster correlation coefficient of 0.05, the design effect is 1.50 giving a required sample size of 378 children and 36 schools in each group. Our proposed sample includes 38 schools/group. We recruited children from the 4-year-old class: in classes with 12 or fewer children, all children were recruited; where there were more than 12 children, a random sample of 12 children were selected. The maximum sample size was 456 children/group.

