#### Statistical methods

The effect of intervention will be examined on an intention-to-treat basis, using multilevel multiple regression models for continuous outcomes and random effects logistical regression models for binary outcomes (and random effect for count outcomes such as Poisson or Negative Binomial if required), to take into account the hierarchical structure of the study. Tester/observer and intervention status (and child age and sex for child-level data) will be entered as fixed effects, and school (and classroom) entered as random effects.

Few studies have reported on mediators of intervention effectiveness in school-based preventative trials. We will explore whether change in teacher depression, self-efficacy and burn-out mediate the effect of intervention on teachers’ use of violence and levels of classroom aggression using standard techniques for multilevel mediation analyses. We will also examine whether teachers’ use of violence and the quality of the classroom environment mediate the effect of intervention on child mental health, self-regulation and attendance. Potential moderators of intervention effectiveness will also be investigated. We will examine whether teachers who use high levels of violence against children at baseline, and whether classrooms characterised by high levels of child aggression at baseline, benefit most from the intervention. We will also examine whether the child's sex moderates the effect of intervention on child mental health, social skills, self-regulation and school attendance.

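### The fallback for the violence primary outcome calls three or four ordered categories a count and names only count models for it; with three categories and high prevalence this makes the test conservative and costs power

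*Protocol article*

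**What the plan says.** The protocol article, Primary outcomes, collects full event data on teacher violence: "Event recording will be used to record each use of corporal punishment, verbal abuse, and other abuse (eg, intimidation) by teachers". The main analysis reduces this to yes or no; the variable "will be coded as a binary variable for analysis, with teachers coded as 1 if they use violence versus 0 if they do not".

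A fallback follows. Its trigger is "If the percentage of teachers using violence is more prevalent than anticipated and/or has wide variability in scores", and in that case "then the variable will be coded as a count using three to four categories to represent the spread of the data". No numeric trigger, cut-points or code values are given.

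Statistical methods lists multilevel regression for continuous outcomes, random-effects logistic regression for binary outcomes, and "and random effect for count outcomes such as Poisson or Negative Binomial if required". It names no ordinal model and no robust or quasi-likelihood variance.

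Sample size sets the test level for each of the two primary outcomes: "we require a significance level of 0.036 in each individual test to keep a Family-Wise Error Rate of 0.05". For violence it states that "90 classes in each group are sufficient to detect a reduction from 60% to 35% with 87% power at 0.05 level of significance". That power statement covers the binary coding only.

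**The concern.** Cutting an event count into three or four bands gives a bounded, ordered score. Calling it a count points the analyst to the count models, and no other model listed suits a code with three or four levels. Poisson regression sets the variance equal to the mean, and the negative binomial can only add variance. Neither can represent a code whose variance is below its mean. That happens when most teachers score above zero, and high prevalence is one of the two conditions that bring the fallback into use.

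One of the two primary tests is at stake. A standard error that is too wide puts the test below its 0.036 level and can miss a reduction that a suitable model would detect in the same data. The estimate also suffers: a ratio of mean category scores depends on where the cuts fall.

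**Working it through.** **Inputs from the protocol article (Sample size).** Prevalence 60% against 35%; 90 classes per group before clustering; three classes per school; ICC 0.1; design effect 1.2; per-test level 0.036. Sidedness is not stated; two-sided is assumed. The article gives no event rate, dispersion, cut-points or code values, so every power figure for the fallback rests on assumptions.

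**1. The plan's own figure.** For 60% against 35% with 90 per group, power at 0.05 is 92.6% (pooled normal approximation) or 90.2% (continuity-corrected). At 0.036 with continuity correction it is 87.5%. The stated 87% therefore matches the per-test level, although the sentence is labelled 0.05; that is a separate matter. Clustering checks: 1 + (3 − 1) × 0.1 = 1.2; 90 × 1.2 = 108; 108 / 3 = 36 schools.

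**2. Three categories coded 0, 1, 2.** Let p be the prevalence of any violence and q the share in the top category.

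- Mean m = p + q; mean square = p + 3q.
- Variance / mean = (p + 3q)/m − m = 3 − 2p/m − m.
- The cut-point moves only m. For p of at least 50% the maximum is at m = √(2p) and equals 3 − 2√(2p).

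This maximum is 1.00 at p = 50%, 0.81 at 60%, 0.47 at 80% and 0.32 at 90%. In an arm with prevalence above 60%, every choice of cut gives variance below the mean.

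**3. Effect on the standard error.** Poisson takes the variance as the mean, while the true variance is also multiplied by the design effect. So model SE / true SE is about 1/√(ratio × 1.2), carrying the design effect over from the binary outcome. A random intercept or negative binomial dispersion term cannot correct a ratio below 1, because each only adds variance. The smallest possible overstatement is:

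| Prevalence | Maximum ratio × 1.2 | Model SE / true SE, at least |
|---|---|---|
| 60% | 0.809 × 1.2 = 0.971 | 1.015 |
| 80% | 0.470 × 1.2 = 0.564 | 1.33 |
| 90% | 0.317 × 1.2 = 0.380 | 1.62 |

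At 60% the error is negligible. At 80% the rejection rate with no effect is at most 2[1 − Φ(2.097 × 1.331)] = 0.5%, against 3.6% nominal.

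**4. Four categories coded 0 to 3.** The same argument gives a maximum of 4 − 2√(3p): 1.32 at 60%, 0.90 at 80%, 0.71 at 90%. It is below 1 only above 75% prevalence. After the design effect, it is below 1 only above (4 − 1/1.2)²/12 = 84%. Two examples:

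- Equal categories: mean 1.5, variance 1.25; 0.833 × 1.2 = 1.00, so there is no error.
- A 40/20/20/20 split: mean 1.2, variance 2.8 − 1.44 = 1.36, so the code is over-dispersed.

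**5. Codes starting at 1.** This raises the mean and leaves the variance unchanged. Equal categories 1 to 3: mean 2, variance 0.667; 0.333 × 1.2 = 0.40; SE ratio 1.58. Equal categories 1 to 4: 0.5 × 1.2 = 0.60; SE ratio 1.29.

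**6. Simulated power.** 36 schools of three classes per arm, two-sided 0.036, 1,000 trials per row. Assumed: negative binomial events, control mean 4 to 10, dispersion parameter 0.4 to 1.5, school log-SD 0.35, a zero category plus quantile cuts. Both category-based columns use the same categories.

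| Control prevalence | Codes | Event-rate ratio | Poisson on code | Ordinal | Negative binomial, raw count |
|---|---|---|---|---|---|
| 62% | 0–2 | 0.38 | 74% | 75% | 95% |
| 82% | 0–2 | 0.46 | 68% | 88% | 97% |
| 95% | 0–2 | 0.56 | 28% | 87% | 97% |
| 62% | 0–3 | 0.38 | 85% | 79% | 95% |
| 82% | 0–3 | 0.49 | 84% | 86% | 94% |
| 95% | 0–3 | 0.58 | 66% | 86% | 94% |

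Recoding from 1 lowers the Poisson power, at 62%, 82% and 95% prevalence, to 32%, 24% and 4% (codes 1–3) and to 70%, 62% and 40% (codes 1–4).

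Rejection with no effect, nominal 3.6%: Poisson on the code 0.0% (0–2, 82%), 1.2% (0–3, 82%) and 3.5% (0–3, 62%). The ordinal model gave 2.9% to 3.4% in these runs, and the negative binomial on raw counts 4.9% to 5.2%.

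A second simulation used other assumptions: 76 schools, mean 5, shape 1.2, school log-SD 0.4, 84% control prevalence, cuts 0 / 1–3 / 4+, and a 40% fall in events. Power was 30% for Poisson and 64% for ordinal. At 75% prevalence it was 37% against 53%. With four categories (0 / 1–2 / 3–5 / 6+) it was 66% against 71%.

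**The case against.** The strongest reply is that the article does not commit itself to a count model for this variable. The reference to count models is a parenthesis with open wording, "random effect for count outcomes such as Poisson or Negative Binomial if required", and does not mention violence. A condensed article may leave cut-points and the final model to an analysis plan. This stands in part: the link is an inference, and absent cut-points alone would be no finding. But the article itself gives the data type as a count, and nothing else it lists fits.

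A reader might also infer that the standard error is always wrong. The documents do not support that. Wide variability alone can trigger the fallback, even at 60% prevalence, and a four-category code can then be over-dispersed, which a negative binomial can represent. With equal 0–3 categories and the plan's design effect the error is nil, and at 62% prevalence with four categories Poisson had more power than the ordinal model.

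Nor can a reader infer that up to half the power is lost. That figure depends on event rates and cuts the article does not give, and it is neither typical nor an upper limit.

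Finally, the main binary analysis is unaffected, and where the variance falls below the mean the error is conservative. Both points stand and limit the severity.

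**Conclusion.** The point holds in a limited form. The fallback gives an ordered category the wrong data type, and the only matching models named do not suit it. For three categories coded 0 to 2 with prevalence above 60%, variance below the mean follows from algebra alone, whatever the cuts. The standard error is then too wide (barely at 60%, by at least a third at 80% given a design effect of 1.2) and false positives are not inflated.

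The power loss against an ordinal model on the same categories is a range under assumed event rates:

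- none or a few points near 60% prevalence with codes from 0, and 2 to 5 points with four categories at 82% to 84%;
- about 20 to 35 points with three categories at 82% to 84%, and about 20 points with four categories at 95%;
- more than half with three categories at about 95%, or with three categories coded from 1.

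The documents fix no single value. This should be fixed, but it is not critical: it arises only if the fallback is used, and the risk is a missed benefit rather than a false claim of one.

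**What to change.** Before the post-test analysis, choose one of two routes.

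(a) Analyse the uncollapsed event count, which the observers already record, with a random-effects negative binomial model. It had the highest power in the simulations (94% to 97%). Two cautions apply: the simulated events were themselves negative binomial, and the test was slightly liberal (4.9% to 5.2% against 3.6%). The fit should be checked and a small-sample reference distribution considered.

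(b) If categories are kept, call them ordered categories in Primary outcomes, and name a random-effects cumulative-logit model in Statistical methods, with school random and arm and observer fixed. Set the numeric trigger and cut-points from the 2015 baseline round, which the Allocation section places before randomisation. The proportional-odds assumption then needs checking.

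Either route costs about a sentence in each of the two sections and needs no new data. Trial status reports the intervention as still under way, so the change can precede the post-test analysis.

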#### Secondary outcomes

In addition to targeting violence prevention, the intervention also aims to promote child and teacher mental health, improve children's self-regulation skills, and improve the quality of the early childhood classroom environment. We have also previously found benefits to children's school attendance. We have secondary outcomes relevant to these aims at the level of the teacher, the classroom and the child. All measures will be conducted by researchers blind to study design, and all questionnaires will be administered in a face-to-face interview.

Classroom level measures. These include independent observations of the class-wide level of children's prosocial skills and of the quality of the classroom environment. Observations will take place over five 20 min intervals concurrently with the observations of class-wide aggression. At the end of each 20 min interval, observers will rate the level of children's prosocial behaviour on a seven-point scale, adapted from one used previously in Jamaican basic school classrooms.^5^ In addition, observers will rate the 10 seven-point scales of the Classroom Assessment Scoring System (CLASS).^21^ The CLASS tool produces summary scores of the quality of the classroom environment across three domains (emotional support, classroom organisation and instructional support). The mean scores over the five observations for each of the four outcomes (prosocial behaviour and three CLASS summary scores) will be used in the analysis. The CLASS predicts young children's social and academic skills.^22^

Teacher-level measures. Teachers will self-report on frequency of depressive symptoms using the Centre for Epidemiological Studies Depression Scale,^23^ teaching self-efficacy using four subscales from Bandura's Teaching Self-Efficacy Scale,^24^ and teacher burn-out using the Teacher Burnout scale.^25^ Strengthening the mental health of teachers of young children is one mechanism to reduce the frequency of dysregulated interactions between teachers and children.^26^

Child-level measures. Child mental health will be measured using the teacher version of the Strengths and Difficulties Questionnaire (SDQ).^27^ The total difficulties score and prosocial score will be used in the analysis.

Child inhibitory control will be measured through direct testing. Inhibitory control is a central component of self-regulation, and represents the ability to suppress impulsive thoughts or behaviours and resist distractions. Self-regulation is important for children's functioning in varied contexts, including classrooms,^28^ and self-regulation in childhood predicts criminal offending, wealth and educational achievement in adulthood,^29^ and hence, represents a key mediator for the effect of intervention on later outcomes.

The three play tests include silly sounds stroop, big/little stroop and bear/frog test. Silly sounds stroop.^30^ Children are presented with pictures of a cat and a dog and told that in the silly sounds game, dogs make the sounds of cats and vice versa. They are then presented with 18 pictures of dogs and cats and asked what sound the animal would make in the silly sounds game.

Big/little stroop.^31^ This test is adapted from the Day-Night Stroop test. Children are presented with pictures of big cats and little cats and are told to say ‘little’ when the tester points to the big cat and ‘big’ when the tester points to the little cat.

Bear/frog test. This test is adapted from the ‘bear/dragon test’,^32^ and involves performing the actions suggested by bear, and inhibiting the actions suggested by frog.

A composite variable of inhibitory control will be created by summing the standardised score of these three tests.

Child attendance will be recorded from school records.

#### Participant timeline

The trial timeline is show in figure 1. The trial is a 4-year study. Initial recruitment and baseline assessments take place in the summer term of the first year of the study. The intervention is delivered to the intervention schools throughout the second year of the study, and post-test measures are collected in the summer term of that year. In the third year of the study, 1-year follow-up measurements will be collected in all schools. The comparison schools receive the intervention in the final year of the study with assessments of teachers’ use of violence, level of class-wide child aggression and prosocial skills, the quality of the classroom environment and teacher depression, self-efficacy and burn-out at the end of the year.

**Figure 1 BMJOPEN2016012166F1:**
[figure not shown]
Trial timeline.

### Sample size

The trial has two primary outcomes: level of class-wide aggression and violence against children. Using Tukey's method of correction for multiple testing,^33^ we require a significance level of 0.036 in each individual test to keep a Family-Wise Error Rate of 0.05.

Level of class-wide aggression. In a parallel group design, 72 classes in each group are sufficient to detect an ES of 0.5 SD, with 81% power at 0.05 level of significance. With a cluster size of three (3 classrooms/school), and assuming an intraclass correlation (ICC) of 0.25, the design effect is 1.5 (design effect=1+(cluster size–1)×ICC)) giving a required sample size of 108 classrooms per group, which yields 36 schools per group. We will recruit 38 schools (114 classrooms) per group (76 schools in total) to allow for 9% teacher loss.

Violence against children by teachers. In a parallel group design, 90 classes in each group are sufficient to detect a reduction from 60% to 35% with 87% power at 0.05 level of significance. With a cluster size of three (3 classrooms/school) and an ICC of 0.1 (based on data from our efficacy trial), the design effect is 1.2, giving a required sample size of 108 classrooms per group, which yields 36 schools in each group. As mentioned above, we will recruit two additional schools per group.

The analyses of the secondary outcomes is considered exploratory, and the significance level of the tests will not be adjusted for comparisons of multiple outcome.

Classroom and teacher-level measures. Similar to the primary outcome of level of classwide aggressions, we have 85% power at a 0.05 level of significance to detect a difference of 0.5 SD on the quality of the classroom environment and on teacher depression, self-efficacy and burn-out.

Child-level measures. In a parallel group design, 252 children in each group are required to detect a difference of 0.25 SD with 80% power at 0.05 level of significance. With 11 children per school, and an estimated intracluster correlation coefficient of 0.05, the design effect is 1.50 giving a required sample size of 378 children and 36 schools in each group. Our proposed sample includes 38 schools/group. We recruited children from the 4-year-old class: in classes with 12 or fewer children, all children were recruited; where there were more than 12 children, a random sample of 12 children were selected. The maximum sample size was 456 children/group.

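### Testing each of the two primary outcomes at 0.036 does not hold the family-wise error rate at 0.05: the rate is about 7.1% if the tests are independent and stays above 5% until their correlation reaches about 0.92

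*Protocol article*

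**What the plan says.** The Sample size section of the protocol article states: "The trial has two primary outcomes: level of class-wide aggression and violence against children". It then sets the threshold: "Using Tukey's method of correction for multiple testing", followed directly by "we require a significance level of 0.036 in each individual test to keep a Family-Wise Error Rate of 0.05". No condition is attached, and no correlation between the outcomes or their test statistics is given anywhere.

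The Primary outcomes section describes two different measures. Teacher violence is event-recorded over two school days and is to be analysed as a binary variable, or in three to four categories if it proves common or widely spread. Child aggression is an observer's seven-point rating, averaged over five 20-minute intervals on one day.

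Power for the two outcomes, before the design effect, is given as "72 classes in each group are sufficient to detect an ES of 0.5 SD, with 81% power at 0.05 level of significance" and "90 classes in each group are sufficient to detect a reduction from 60% to 35% with 87% power at 0.05 level of significance". The same section treats the secondary outcomes as exploratory and leaves them unadjusted, so the 0.036 rule is the trial's only multiplicity control.

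**The concern.** For two tests, the per-test level that holds 5% under any dependence is 0.05/2 = 0.025. The level that holds it under independence is 1 − 0.95^(1/2) = 0.0253. A level of 0.036 is well above both, so it can hold 5% only if the two test statistics are very strongly correlated, and the article does not claim that they are.

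At stake is the confirmatory claim. Per-test levels chosen to control a family-wise rate imply that each outcome can be claimed separately. If the best of the two results falls just under 0.036, the trial would report a finding as meeting 5% family-wise control when it does not.

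**Working it through.** **Inputs.** From the Sample size section: two primary outcomes; 0.036 per test; target 0.05; aggression 72 classes per group, 0.5 SD, 81% power; violence 90 classes per group, 60% versus 35%, 87% power. Assumed, because not stated: two-sided tests and jointly normal test statistics. The correlation ρ is not given, so a range is shown.

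**Step 1: reproduce 0.036.** The Tukey square-root rule gives 1 − (1 − 0.05)^(1/√2) = 0.0356, which rounds to 0.036. Bonferroni (0.025) and Šidák (0.0253) do not give this figure.

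**Step 2: family-wise error at 0.036 each, both nulls true.** Under independence: 1 − (1 − 0.036)² = 1 − 0.9293 = 7.07%. The upper bound under any dependence is 2 × 0.036 = 7.2%. For correlation ρ, with c the two-sided 0.036 critical value, the rate is 1 − P(|Z1| < c and |Z2| < c) for a bivariate normal pair:

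| ρ | family-wise error |
|---|---|
| 0 | 7.07% |
| 0.3 | 6.91% |
| 0.5 | 6.61% |
| 0.6 | 6.39% |
| 0.7 | 6.10% |
| 0.8 | 5.71% |
| 0.9 | 5.13% |
| 0.95 | 4.70% |

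The rate equals 5% at ρ ≈ 0.92 (0.91 with the unrounded 0.0356; about 0.90 if the tests were one-sided).

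**Step 3: the level behind the stated power.** For aggression, a two-sample t-test with 72 per group and 0.5 SD has 81.1% power at 0.036 and 84.6% at 0.05. The stated 81% therefore matches 0.036, not its printed label. For violence, 90 per group gives 87.5% at 0.036 and 90.2% at 0.05 with continuity correction; without it, 90.4% and 92.6%. The stated 87% is again closest to 0.036. The same section quotes 85% at 0.05 for classroom-level secondary outcomes at 0.5 SD, which fits this reading. Below, 81% and 87% are taken as power at 0.036.

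**Step 4: power under Holm.** An outcome is rejected if its p ≤ 0.025, or if its p lies between 0.025 and 0.05 and the other p ≤ 0.025. With the test means set to give 81.05% and 87.0% power at 0.036, power is 76.9% (at 0.025) and 84.5% (at 0.05) for aggression, and 83.7% and 89.7% for violence. Under independence:

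- aggression: 0.769 + (0.845 − 0.769) × 0.837 ≈ 83.3%
- violence: 0.837 + (0.897 − 0.837) × 0.769 ≈ 88.3%

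At ρ = 0.5, simulation with 2 million draws gives about 82.6% and 87.2%. If only one effect is real, power is about 77% (aggression) or 84% (violence).

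**Step 5: how often the rules differ to the trial's advantage.** The 0.036 rule claims something that Holm does not only when the smaller p lies between 0.025 and 0.036. Under the planned effects this happens in about 1.3% of trials at ρ = 0 and 2.2% at ρ = 0.5.

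**The case against.** The rule is a named, cited and prespecified method, 0.036 is its correct output, and it is stricter than testing both outcomes at 0.05. The outcomes are measured in the same classrooms, and the second-day violence observations follow the schedule of the class-wide observations, so some positive correlation is plausible and 7.1% is the top of the range. The excess is about 2.1 points under independence and cannot exceed 2.2. No sample size or estimate changes. All of this stands, and it lowers the weight of the point. It does not make the sentence true: a correlation of about 0.92 between acts by teachers and a rating of children's behaviour has no support in the article.

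Three stronger readings are tempting and are not supported:

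- **That the error rate is 6.6–7.1% for any correlation below about 0.9.** That range covers only correlations from 0 to about 0.5. Beyond that the rate falls steadily to 5% at about 0.92.
- **That every primary p value between 0.025 and 0.036 would be over-claimed.** Under Holm, once the smaller p is at or below 0.025, the other may be claimed up to 0.05. Only the smaller p value is affected.
- **That the power comparison needs no assumption.** The article labels 81% and 87% as power at 0.05. Taken as labelled, aggression power would be roughly 79% under Holm and about 72.5% at a fixed 0.025.

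**Conclusion.** The statement that 0.036 per test keeps the family-wise error rate at 0.05 is wrong as written. The fault lies in the property claimed for the rule; the arithmetic that produced 0.036 is right. The size depends on a correlation that the article does not give, as shown in the table, and the result rests on two-sided tests and jointly normal statistics. One-sided testing would move the crossing point only to about 0.90.

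The article does not spell out that success on either outcome suffices. The conclusion relies on the reading that two separately tested primary outcomes under a family-wise rule may each be claimed, which is the only reading under which such a rule is needed.

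This should be fixed. It is not a fatal flaw, because the excess error is at most about 2 percentage points and the practical difference between the rules is confined to a small share of trials.

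**What to change.** Replace the 0.036 rule with Holm: compare the smaller primary p value with 0.025 and, if it passes, the other with 0.05. This holds 5% under any correlation. Restate power under that rule, and state the significance level to which the 81% and 87% belong.

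The cost is a sentence or two of text and no extra schools. On the reading that 81% and 87% are power at 0.036, power is the same or slightly higher when both planned effects are real and the correlation is between 0 and 0.5. The loss comes if only one effect is real: 81% becomes about 77% for aggression, or 87% becomes about 84% for violence.

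A fixed 0.025 for each outcome is also valid, but it incurs that loss in every case, with aggression power about 77%. If 0.036 is kept, the claim that it holds 0.05 should be withdrawn and the actual range reported.

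The Trial status section reports the intervention as under way, and the Outcome measures section places post-test in the summer term of 2016. On the article's own timeline, the rule could be changed before post-test data exist.
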